**Methods:**

A 2-arm randomized controlled trial with a parallel assignment of 1:1, with no blinding of study intervention, was performed. Eligible participants are consenting people living with HIV aged 18-29 years who receive HIV care at the study center and whose mobile phones support WhatsApp. Following informed consent and a baseline survey on clinical and personal preferences (eg, timing and frequency of messages), participants are randomized to the control group (messages designed by the research team) or to the experimental group (messages designed by participants), stratified by sex, educational level, current ART intake, and history of ART abandonment. Participants in both groups receive up to 3 WhatsApp messages per week for 16 weeks. ART adherence, the primary outcome, is measured using the Simplified Medication Adherence Questionnaire (SMAQ) at 4, 8, 12, and 16 weeks. Monthly feedback questionnaires on user experience are also administered. The WhatsApp chat format allows two-way communication between participants and the research team throughout the study. We will compare ART adherence between 2 groups at 16 weeks under the intention-to-treat principle, with no interim analysis planned. Based on an estimated 10% difference in adherence, 78.9% power, and a 2-sided α of .05, the target sample size was set at 120, later increased to 131 to include a 2-week pilot phase.

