### Study Design

A randomized controlled trial with 2 arms and a 1:1 assignment ratio will be conducted.

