### Sample Size Determination

The sample size calculus considered a 95% CI and the assumption of a 10% difference in optimal ART adherence between study groups (90% in the self-designed group versus 80% in the standardized group by the end of the study). Accounting for a power level of 78.9%, the obtained result was 120 (EPIDAT 4.0). To account for a 2-week pilot phase, we increased the sample size to 131 participants.

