### Outcomes

The primary outcome is ART adherence, measured by the SMAQ questionnaire at 16 weeks of intervention and adjusted for the effect of covariables. The SMAQ questionnaire evaluates medication adherence. It provides a dichotomic result of adherence (yes or no) and a semiquantitative estimate of adherence. >95% adherence is considered as “yes” and <95% as “no.”

The secondary outcomes are (1) ART adherence measured by the SMAQ Questionnaire at 4, 8, and 12 weeks of intervention; (2) loss to follow-up; (3) time of permanence in the study; and (4) metrics on the use of a bidirectional platform for intervention delivery.

Since the SMAQ provides a dichotomic result of adherence (yes or no), we will report the percentage of participants’ adherent to ART per study group at 4, 8, and 12 weeks of intervention.

To measure loss to follow-up, we defined it as either (1) participants not responding to messages for ≥30 continuous days since receiving the intervention and not responding to messages or questionnaires at the end of their intervention period (*t*=16), or (2) participants not responding to messages for ≥30 continuous days since receiving the intervention and not reading their messages until the end of their intervention period. We will measure it from the start of the delivery intervention until the completion of the study.

Time of permanence in the study will be measured from the first date of intervention delivery (baseline) until loss to follow-up or study completion (16 weeks). We will describe this result's median and interquartile range in both study arms.

To assess the use of the bidirectional platform, we will report frequencies, percentages, and means with an SD of messages and questionnaires programmed for sending, sent, received, read, and answered by participants. Also, the frequencies and percentages of different process indicators self-reported by participants.

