### Data Analysis Plan

The primary outcome variable is ART adherence, primarily measured as a binary variable defined by the SMAQ results at 4, 8, 12, and 16 weeks of intervention. For the analysis of the primary outcome, and with an intention-to-treat approach, we will compare between both study groups the proportion of participants adherent to ART at 16 weeks of intervention with bivariate (chi-square) and multivariate (logistic regression) analyses. We will build the multivariate logistic regression model with a stepwise approach (forward selection and backward deletion), adding 1 explanatory variable at a time and starting with the explanatory variables with the highest theoretical value and strength of association with the primary outcome in bivariate analyses. At each step of model building, we will check variations in the reported odds ratios and standard errors to define the retention or removal of explanatory variables. Irrespective of bivariate association, the study group variable and potential confounders, notably history of ART abandonment, ART pick-up visits during the study period, and time of permanence in the study, will be entered into the model. We will test the final model fit with Hosmer and Lemeshow goodness-of-fit test and report results with adjusted odds ratios and 95% CIs. Preliminary outcome analyses will not be performed since they require multiple measurements, and the intervention is relatively short. We will not perform multiplicity adjustments.

With mixed models for repeated measures, we will explore the changes in ART adherence, as determined by SMAQ, from baseline to 4, 8, 12, and 16 weeks on the intention-to-treat population, with no imputation of missing data. In this model, the change from baseline value will be the dependent variable, with participant random effect and baseline ART adherence, intervention group, and measurement time as the primary fixed factors. We will check linearity assumptions for time and use participants’ unstructured covariance structure. Two-sided 95% CIs for the mean change within each study group will be calculated.

To compare the time of study permanence in both study groups, we will perform survival analysis and compare hazard ratios for study loss to follow-up between study groups, according to the study definitions. This definition lets us know how many participants are active each week of intervention.

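### The adjusted primary model is built by stepwise selection and odds-ratio movement with no threshold, and is not ranked against the chi-square test, so its p-value and 95% CI lack their nominal properties

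*Protocol article*

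**What the plan says.** The Data Analysis Plan compares the proportion adherent at 16 weeks, by intention to treat, with both a chi-square test and a multivariable logistic regression. Neither is named as decisive, and multiplicity adjustment is ruled out.

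On the regression it says: "We will build the multivariate logistic regression model with a stepwise approach (forward selection and backward deletion), adding 1 explanatory variable at a time". Entry starts with the variables of highest theoretical value and strongest bivariate association with the outcome. Retention works as follows: "At each step of model building, we will check variations in the reported odds ratios and standard errors to define the retention or removal". No size of change is given that would keep or remove a variable.

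Study group is always entered. So are potential confounders, of which three are named: history of ART abandonment, ART pick-up visits during the study, and time of permanence in the study. The final model supplies the adjusted odds ratios and 95% CIs.

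The Outcomes section describes the primary outcome as "adjusted for the effect of covariables", without listing the covariables. That wording points to the adjusted model as the headline result. The paragraph after the main analysis text says that the analyses will be done with study groups masked.

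**The concern.** In a randomised comparison the baseline covariates need not be discovered from the outcome data. Randomisation removes systematic confounding, and prognostic variables can be named in advance. Here the covariate set depends on the same outcomes that the model then tests. The reported standard error is computed as if that set had been fixed beforehand.

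The retention rule adds a second difficulty. The odds ratios being watched may include the one for study group. A treatment odds ratio changes when a prognostic covariate is added even if the covariate is perfectly balanced between arms (non-collapsibility). Movement is therefore not evidence of confounding and is not a sound reason to keep or drop a term.

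Third, there are two candidate primary results and no rule for which one counts. If they fall on opposite sides of 0.05, the protocol does not settle the conclusion.

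**Working it through.** **Inputs from the protocol.** Two-sided alpha 0.05 (abstract); allocation 1:1 (Study Design); adherence "90% in the self-designed group versus 80% in the standardized group by the end of the study" and N = 120, later 131 (Sample Size Determination). The protocol gives no candidate list, entry or removal threshold, or size of odds-ratio change.

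**The plan's own figure.** With pooled variance, n per arm = [1.96·√(2·0.85·0.15) + 0.803·√(0.8·0.2 + 0.9·0.1)]² / 0.10² = (0.990 + 0.402)² / 0.01 ≈ 194, that is 388 in total. The stated 120 at 78.9% power is not reproduced; 60 per arm gives 33%. That is a separate matter. Only the two adherence rates are used below.

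**Expected non-adherent participants.** 60·0.10 + 60·0.20 = 18 of 120. For 131, 131·0.15 ≈ 19.7, about 20. Study group plus the three named forced covariates make four terms: 18/4 = 4.5 and 20/4 = 5 non-adherent participants per term, before any selection.

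**Simulation under no treatment effect.** Assumptions:
- 10 candidate baseline covariates, of which either none or 3 are prognostic (log odds ratio 0.6 each).
- Intercept 1.75, so adherence is 1/(1 + e^−1.75) = 0.85 with covariates at zero.
- Study group always in the model; the plan's other forced terms were not imposed.
- 2,000 replicates per setting; Monte Carlo standard error √(0.05·0.95/2000) ≈ 0.005.

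Rules compared: p-value stepwise (enter at 0.10, remove at 0.15), and a change-in-estimate rule that keeps a covariate if the treatment odds ratio moves by at least 10%.

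| Type I error at nominal 0.05 | N=120, none prognostic | N=120, 3 prognostic | N=131, 3 prognostic |
|---|---|---|---|
| Chi-square | 0.052 | 0.052 | 0.057 |
| Fixed 3-covariate model | 0.049 | 0.046 | 0.052 |
| P-value stepwise | 0.052 | 0.064 | 0.067 |
| Change in treatment odds ratio | 0.056 | 0.076 | 0.068 |
| Smaller p of chi-square and stepwise | 0.061 | 0.080 | 0.083 |
| Smaller p of chi-square and change-in-estimate | 0.064 | 0.086 | 0.084 |
| Worst case: keep whatever enlarges the treatment z | 0.099 | 0.140 | 0.134 |

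A second simulation used 131 participants, 85% adherence, 12-20 candidates with 3 prognostic, entry at p<0.10, and 1,500 runs per setting (standard error about 0.006). Stepwise gave 0.063, 0.064, 0.081 and 0.069. The fixed three-covariate model gave 0.053, 0.051, 0.047 and 0.035. The unadjusted test gave 0.027-0.043.

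**Reading.** With prognostic covariates, a mechanically selected model runs at about 6-8%, so its nominal 95% interval covers a true null about 92-94% of the time. Taking the better of two results gives about 8-9%. With no prognostic covariates the selected model is close to nominal, at 5.2-5.6%.

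**The case against.** Several points on the other side have weight.

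- **Theory and forced terms.** Entry is guided by theoretical value as well as observed association, and study group stays in throughout. This stands, and it is one reason why the excess under mechanical selection is modest.
- **Which odds ratio is watched.** A reader might infer that selection runs on the treatment effect. The text does not say whose odds ratios are inspected, and watching coefficients and standard errors can also be a check for collinearity. The treatment odds ratio is not excluded, but its use is not shown. The 13-14% worst case therefore describes what the wording would permit, not what is planned.
- **Masking.** A reader might infer that an unblinded team chooses the model. The absence of blinding concerns delivery of the intervention, and the Data Analysis Plan says that study groups are masked at analysis, though how far that sentence reaches is open to argument. Masked labels do not cure the problem: the size of the group odds ratio stays visible at each step, and mechanical selection raises the error rate without anyone looking.
- **The simulations rest on assumptions.** This stands. In two of the four settings of the second set the gap to the fixed model is only 1.0 and 1.3 points. The figures show direction and rough size only.
- **Crude and adjusted results are routinely reported together.** True, and the Outcomes wording leans toward the adjusted one. It does not say that the adjusted result decides, and the adjusted model is the one left open to selection.

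**Conclusion.** The point holds for the selected model and for the open choice between two primary results. This is a method that the protocol states, not a detail left to a separate analysis plan. Under the assumptions above, type I error is about 6-8% after selection and 8-9% if the better result is taken, against about 5% with fixed covariates. The exact figure cannot be derived from the protocol, because it gives neither candidates nor thresholds. With no prognostic covariate the excess is small, but adjustment would then also have little purpose.

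It would go too far to conclude that every confirmatory p-value in the trial is invalid. The chi-square test is untouched by selection and kept its level in both sets of simulations (0.052-0.057 and 0.027-0.043).

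Sparse data are a second weakness of the same model: 18-20 non-adherent participants cannot support a search among covariates.

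**What to change.** Remove the stepwise procedure and the odds-ratio and standard-error retention rule from the primary analysis. Name one primary analysis: a logistic model with study group and a short fixed set of covariates measured before randomisation and already collected. The natural set is the four stratification factors (sex assigned at birth, educational level, current ART intake, previous ART abandonment) and, where it is defined, baseline SMAQ.

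Even this set means at least six terms, or 18/6 = 3 expected non-adherent participants per term, so state in advance that Firth penalisation will be used if cells are sparse. The two forced covariates that arise during follow-up (ART pick-up visits and time of permanence) are not pre-randomisation variables and fall outside this set.

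Label the chi-square test supportive. If predictors of adherence are of interest, keep a stepwise model as a separate exploratory analysis. A standardised risk difference with 95% CI is an optional addition, since the design hypothesis is a 10-point difference.

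The protocol reports data curation under way in February 2025, so the change should be dated and made before any group comparison is seen. It costs analysis-plan wording and the freedom to choose the model afterwards.

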### Study Procedures—Preimplementation Phase

First, during the study's design, we consulted with health staff to better respond to the study’s population needs without disrupting routine HIV program operations. Once the study design was completed, the coordination was intended to communicate study standard procedures and facilitate the study's implementation. Our institutional review board (IRB) approved the full study protocol in July 2023. Then, we designed the web-based study platform with Infobox Latinoamérica, a Peruvian IT company. The web-based study platform is integrated with WhatsApp business and supports the delivery of personalized and standardized messages, a Chatbot for mass-sending questionnaires and continuous chat with participants. The Infobox provides technical support during the study as required.

The principal investigator (PI) completed the web-based training on BCT-Taxonomy to design the standardized messages. He created 44 standardized messages, each corresponding to one of 14 selected BCT categories, though the final format considered elements of other behavior change theories (health belief model, social support theory, and social cognitive theory). The number of standardized messages minimized the chance of participants receiving repeated messages during the study period. Table S1 in Multimedia Appendix 1 lists all standardized messages with their corresponding BCTs in the order those messages are sent to participants.

We created the randomization sequence using the REDCap (Research Electronic Data Capture) randomization module (REDCap Consortium); sex assigned at birth, educational level, current ART intake, and previous ART abandonment were the criteria for stratified randomization.

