### Data Collection

For this study, data collection and management use REDCap electronic data capture tools hosted at Universidad Peruana Cayetano Heredia [24]. The enrollment form collects participants’ baseline sociodemographic data, history of ART, strategies for taking ART, assessment of their adherence with the SMAQ, depression screening, stigma, an evaluation of their satisfaction with the health services provided at the study center, and a measurement of their knowledge about ART and adherence. For participants allocated to the self-designed messages arm, we also register their created messages in REDCap. In total, 4 members of the research team are involved in data collection. The PI trained them with mock interviews and a web-based course on using REDCap.

We used an intermediate Excel file hosted in a secured drive to schedule messaging and questionnaire delivery per participant through the web-based study platform. This file contains the identification codes, a list of messages, and the date and time of sending.

The web-based study platform collects CSV file data on every message and questionnaire scheduled, sent, received, read, and answered per participant and chat sessions with providers. The records include anonymous hour-dated logs of all conversation contents with participants, including reasons for adding, modifying, or eliminating messages in the self-designed group and responses to study questionnaires.

To obtain the total number of eligible patients who meet eligibility criteria, independent of whether they are invited to participate, we collect routine data from the study center regarding the number of outpatient consults and patients in the age group of interest who pick up ART during the study period.

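### Of the four stratification factors and baseline SMAQ, the primary analysis names only ART abandonment for forced entry; the rest are left to stepwise selection, at a modest cost in precision

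*Protocol article*

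**What the plan says.** Under Study Procedures—Preimplementation Phase, the article states that "sex assigned at birth, educational level, current ART intake, and previous ART abandonment were the criteria for stratified randomization". Under Data Collection, the enrolment form includes an "assessment of their adherence with the SMAQ". The Implementation Phase section places the baseline questionnaire before randomisation.

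The Data Analysis Plan makes the week-16 comparison with a chi-square test and a multivariable logistic regression built by forward and backward steps. Candidates are ordered by theoretical value and by observed association with the outcome. The sentence on variables that enter regardless begins "Irrespective of bivariate association, the study group variable and potential confounders, notably history of ART abandonment". It then names pick-up visits made during follow-up and the time a participant stays in the study. Baseline adherence is a stated fixed factor only in the repeated-measures model, which is described as exploring change over time.

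**The concern.** When randomisation is balanced on prognostic factors, a test that ignores them uses a standard error that is too large for the design, so the chi-square is somewhat conservative. Baseline SMAQ was not a stratification factor. A chance difference between arms in baseline adherence is therefore not controlled by design, and under this plan it is controlled in the analysis only if selection happens to keep the variable.

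The plan is also inconsistent with itself. Four factors were thought important enough to balance on, and baseline adherence important enough to fix in the repeated-measures model, yet the primary model follows neither decision. At stake is some precision in a trial that has little, and an adjustment set that depends on the week-16 results.

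**Working it through.** **Which variables are fixed.** Of the five design or baseline variables:

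| Variable | Stratification factor | Named for forced entry in the primary model |
|---|---|---|
| Sex | yes | no |
| Educational level | yes | no |
| Current ART intake | yes | no |
| Previous ART abandonment | yes | yes |
| Baseline SMAQ | no | no (fixed only in the repeated-measures model) |

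**How much precision there is.** The inputs are "90% in the self-designed group versus 80% in the standardized group by the end of the study" (Sample Size Determination), a two-sided α of 0.05 and 78.9% power (abstract), and 1:1 allocation. With the pooled normal approximation and mean proportion 0.85:

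- n per arm = [1.96·√(2·0.85·0.15) + 0.803·√(0.09 + 0.16)]² / 0.10² = (0.990 + 0.4015)² / 0.01, which rounds up to 194 per arm, or 388 in total. The stated 120 does not reproduce.
- Power at 60 per arm: Φ[(0.10 − 1.96·√(0.255/60)) / √(0.25/60)] = Φ(−0.43) = 33%.
- Power at 131 (65.5 per arm): Φ(−0.36) = 36%.

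**What fixing all five covariates would add.** The documents give no association between baseline and week-16 SMAQ, so it was varied. Assumptions: baseline adherence 60%; four binary stratification factors with prevalences of 20 to 50% (16 strata, permuted blocks); marginal adherence 80% and 90%; baseline odds ratio (OR) 2, 4 or 8, with stratum effects growing alongside; 2,000 simulated trials per scenario. The logistic models used likelihood-ratio tests. Efficiency is the variance of the unadjusted risk difference divided by that of the five-covariate standardised risk difference.

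| N | Baseline OR | Power: chi-square | Power: abandonment only | Power: all five | Efficiency |
|---|---|---|---|---|---|
| 120 | 2 | 0.318 | 0.337 | 0.352 | 0.99 |
| 120 | 4 | 0.333 | 0.353 | 0.386 | 1.04 |
| 120 | 8 | 0.361 | 0.378 | 0.438 | 1.13 |
| 131 | 2 | 0.377 | 0.392 | 0.416 | 0.99 |
| 131 | 4 | 0.362 | 0.383 | 0.420 | 1.05 |
| 131 | 8 | 0.342 | 0.364 | 0.436 | 1.11 |

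At N = 120 the power gain is 2 to 6 points over abandonment only and 3 to 8 over the chi-square. At N = 131 it is 2 to 7 and 4 to 9. The simulation error of each power figure is about √(0.35·0.65/2000) = 1 point.

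**How much of the gain is real.** Under the null, the five-covariate test rejected 5.4 to 6.6% of the time. With covariates of no prognostic value at N = 120, its power still read 0.347 against 0.313 for the chi-square, although efficiency was 0.995. About 3 points there are inflation, not information. The chi-square rejected 3.9 to 5.3% under the null in the scenarios with prognostic factors, so it is slightly conservative at most.

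**Events available.** At 90% and 80%, expected non-adherent participants are 60·0.10 + 60·0.20 = 18 at N = 120, and 65.5·0.30 = 19.7 at N = 131. A model with arm, sex, education, abandonment and a three-level baseline category has six terms: 18/6 = 3.0 and 19.7/6 = 3.3 events per parameter, before any dropout.

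**The case against.** The strongest reply is that nothing is excluded. The word *notably* leaves the forced list open, and the ordering rule would bring a strong baseline predictor in early. The article also refers to a separate statistical analysis plan, which could give the full list. This stands in part: the four variables are not barred, only not fixed. It also means that the simulated abandonment-only model may overstate the loss, since the stepwise model could recover some of it. But the article does commit to data-driven selection, and that is a choice, not an omitted detail.

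Two stronger readings are tempting. First, a reader might assume a baseline to week-16 correlation of 0.3 to 0.5 and infer from 1/(1 − r²) that adjustment is worth 10 to 33% more participants, lifting power at 131 from 36% to between 39% and 46% at no cost. The documents support no such correlation. With 85% adherent at week 16, r = 0.3 already needs an odds ratio of about 5 to 8. An r of 0.5 needs about 16 at 80% baseline adherence, 21 at 70% and 138 at 60%, and cannot occur at 50%. The range must include zero. Nor is adjustment free, with about three events per parameter.

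Second, a reader might say that the planned logistic model has standard errors that are too large. That describes the chi-square. In logistic regression, adding a prognostic covariate generally raises the standard error of the log odds ratio. Power improves because the conditional odds ratio moves further from 1.

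**Conclusion.** The point holds as a pre-specification fault of modest size. One of five relevant baseline variables is named for forced entry, and the primary result's adjustment set is otherwise chosen from the outcome data. Fixing all five is worth about 0 to 13% in efficiency if the baseline odds ratio lies between 2 and 8. The corresponding power gain is the 2 to 8 points at N = 120 (2 to 9 at N = 131) shown above, some of it inflation. If baseline SMAQ predicts weakly, the gain is essentially nil. These figures rest on assumed prevalences and stratum effects and on complete week-16 response.

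No version of this adjustment brings power near 78.9%. That the sample size does not follow from its own inputs is a separate and larger problem. So is the forced entry of two variables measured after randomisation.

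**What to change.** Before any analysis by unmasked arm, pre-specify one primary model without stepwise selection and with baseline covariates only, all as main effects:

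- study arm;
- sex assigned at birth;
- education, collapsed to two groups;
- previous ART abandonment;
- a single baseline category (adherent, not adherent, not on ART) that combines baseline SMAQ with current ART intake and replaces a separate intake term.

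Drop pick-up visits and time in the study, and say why: both are measured after randomisation and may be affected by arm. The Discussion itself expects longer stay in the self-designed group, so adjusting for it could remove part of the effect or bias it.

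Because events are sparse, report the arm effect as a standardised risk difference or use a penalised (Firth) fit, not plain logistic regression. Keep the chi-square as a supporting unadjusted result.

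The cost is plan wording and a little more analysis work, since the article has these data collected at enrolment. The remaining risk is sparse-event bias if plain logistic regression is used after all.

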## Discussion

Guided by the application of BCTs, we hypothesize that self-designed messages may be more effective in improving adherence to ART than standardized messages. Therefore, we aim to evaluate the effectiveness of a mobile phone messaging intervention with WhatsApp to improve adherence to antiretrovirals in young people living with HIV who receive routine HIV care at a public health facility in Lima and assess if there is a difference in effectiveness between the 2 types of messages tested. In a setting with still inceptive use of mHealth, our study protocol will provide valuable information on associations between several covariables, ART adherence, and participants’ experience with our pilot mHealth intervention.

Self-designed messages offer customization features that may enhance participant engagement with the intervention and increase its efficacy [26,27]. Therefore, we expect participants in the self-designed messages arm to have improved adherence compared to the standardized messages arm. Some subgroups may benefit more from the intervention, although it is beyond the scope of this study to compare differences between study arms and potential effect size. Given the potential personal customization component, we hypothesize that the self-designed arm will have an increased median time of permanence in the study and lower loss to follow-up. We also anticipate that loss to follow-up may hinder the statistical significance of results for the primary outcome and ART adherence measured at 4, 8, and 12 weeks of intervention for both study arms.

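### The primary logistic model forces in two variables measured after randomisation, so its adjusted odds ratio does not estimate the promised intention-to-treat effect

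*Protocol article*

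**What the plan says.** The Outcomes section ties the primary outcome to an adjusted result: "The primary outcome is ART adherence, measured by the SMAQ questionnaire at 16 weeks of intervention and adjusted for the effect of covariables". The Data Analysis Plan, under an intention-to-treat approach, compares the arms "at 16 weeks of intervention with bivariate (chi-square) and multivariate (logistic regression) analyses". The logistic model is built stepwise, but some terms are exempt from selection: "Irrespective of bivariate association, the study group variable and potential confounders, notably history of ART abandonment", and then "ART pick-up visits during the study period, and time of permanence in the study, will be entered into the model". Results are to be reported as adjusted odds ratios with 95% CIs.

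The Outcomes section also lists, among the secondary outcomes, "3) time of permanence in the study", and defines it: "Time of permanence in the study will be measured from the first date of intervention delivery (baseline) until loss to follow-up or study completion" at 16 weeks. The Data Analysis Plan compares it between arms by survival analysis. In the Discussion, "we hypothesize that the self-designed arm will have an increased median time of permanence in the study and lower loss to follow-up".

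**The concern.** Of the three named potential confounders, only history of ART abandonment is fixed before randomisation. The other two are observed while the messages are being delivered. Randomisation already deals with confounding of the comparison between arms, so adjusting for later variables cannot remove any. It can do two other things:

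- If the intervention changes the variable and the variable is linked to adherence, holding it fixed takes part of the intervention's effect out of the estimate.
- If something unmeasured, such as motivation, drives both the variable and adherence, and the intervention shifts the variable, conditioning on it makes the arms differ in motivation at each level of the variable. This distorts the estimate even when the intervention has no effect on adherence.

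For permanence the article contradicts itself: the same variable is an expected effect of the intervention and a covariate held fixed when that intervention is evaluated. What is at stake is the adjusted odds ratio, one of the two planned analyses of the primary outcome.

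**Working it through.** **1. When each forced term is fixed**

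| Term | Timing | Role elsewhere in the article |
|---|---|---|
| Study group | randomisation | the comparison itself |
| History of ART abandonment | baseline | stratification factor |
| ART pick-up visits during the study | after randomisation | none stated; dispensing is usually monthly and depends on stocks (Setting) |
| Time of permanence | after randomisation | secondary outcome; hypothesised to be longer in the self-designed arm |

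**2. What permanence can contribute, given its definition.** Both limbs of the loss-to-follow-up definition require at least 30 days without response. The first adds no response to messages or questionnaires at the end of the period; the second adds not reading messages until the end. A participant who answers the week-16 SMAQ practically never meets either limb and so has permanence of 16 weeks.

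- Among week-16 responders, the covariate is nearly constant. It adjusts for almost nothing.
- If non-responders were counted as non-adherent, short permanence would nearly determine the outcome (separation).

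It is not a usable covariate either way.

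**3. Size, illustrated for pick-ups.** The planning rates in Sample Size Determination are 80% and 90%: a difference of 10 points and an odds ratio of (0.90/0.10)/(0.80/0.20) = 9/4 = 2.25. The article gives no effect on pick-ups, so everything below is assumed:

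- unmeasured motivation U is standard normal;
- pick-ups are binomial out of 4 (monthly dispensing over 16 weeks), with probability expit(1 + 0.8U + d × arm);
- logit of adherence = a + b × arm + 0.6 × pick-ups + 0.7U, with a and b set so that the arms have 80% and 90% overall;
- for the no-effect case, logit of adherence = a + 0.9U, 85% adherent overall, with no effect of arm or of pick-ups.

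A logistic model with arm and pick-ups is then fitted in a very large sample. The adjusted difference is the model's risk difference averaged over everyone's pick-ups.

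| d | Mean pick-ups, standardised → self-designed | Adjusted OR | Adjusted difference | Adjusted OR, no true effect |
|---|---|---|---|---|
| 0 | 2.83 → 2.83 | 2.56 | about 10 points | 1.00 |
| 0.1 | 2.83 → 2.90 | 2.35 | about 9 points | 0.97 |
| 0.2 | 2.83 → 2.97 | 2.17 | about 8 points | 0.94 |
| 0.5 | 2.83 → 3.16 | 1.73 | about 6 points | 0.84 |
| 0.8 | 2.83 → 3.33 | 1.42 | about 4 points | 0.78 |

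The odds ratios carry simulation error of about 0.01. With d = 0, the odds ratio rises from 2.25 to 2.56 only because odds ratios are non-collapsible; the risk difference does not move. The difference column is therefore the cleaner guide to bias.

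**4. A second set of assumptions.** Here a continuous post-randomisation covariate has a log-odds slope of 0.5 or 1.0 on adherence, with or without a shared unmeasured cause. Its shift is expressed in units of its residual SD.

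| Shift | Adjusted OR |
|---|---|
| 0.25 | 1.95 to 2.09 |
| 0.5 | 1.50 to 1.78 |
| 0.75 | 1.05 to 1.58 |

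With no shift, the difference stays at about 10 points. With no true effect, no effect of the covariate on adherence, a shift of 0.5 and a shared cause, the adjusted odds ratio is 0.81.

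**The case against.** The strongest reply is that the unadjusted comparison survives. The chi-square test is planned under intention to treat, the Abstract describes the primary comparison without mentioning adjustment, and the Outcomes section does not name these two variables. This stands. A reader might infer that the trial's whole primary result is biased, but the documents do not support that: the problem lies in one of two planned analyses. It is not harmless, because the Outcomes section attaches adjustment to the primary outcome and nothing says which result decides if the two disagree.

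A reader might also infer that the intervention is meant to change pick-ups. No section says so, and the Setting section makes dispensing depend on stocks, so pick-ups partly reflect supply. An effect is plausible for an adherence intervention, but it is an inference. If there is none, the tables show no attenuation.

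Third, if permanence is nearly constant among week-16 responders, it drops out and does little damage there. That is correct for an analysis of responders, and it means permanence serves no purpose in that model. Counting non-responders as non-adherent is only a possibility considered here; the article does not state it.

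Last, the no-effect column assumes that messages raise pick-ups, that adherence is unchanged, and that pick-ups do not themselves affect adherence. It shows that spurious harm is possible, not that it is likely.

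A separate analysis plan could add detail, but it would have to reverse an explicit covariate specification.

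**Conclusion.** Wrong as written. Two post-randomisation variables are forced into the primary logistic model as confounders, which they cannot be in a randomised comparison. For permanence, the conflict with the article's own secondary outcome and hypothesis is explicit; for pick-ups, the objection rests on timing and on a plausible but unstated effect. The adjusted odds ratio therefore does not estimate the intention-to-treat effect. The chi-square comparison does not share the problem.

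The size cannot be derived from the documents. In the illustrative pick-up model, a true 10-point difference is estimated at anything from about 10 points (no shift in pick-ups) down to about 4 points (mean rising from 2.83 to 3.33). With no true effect, the adjusted odds ratio runs from 1.00 down to about 0.78. These figures depend on the assumed shift and on the assumed links between motivation, pick-ups and adherence. None of them measures the effect of including permanence.

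**What to change.** - Remove ART pick-up visits and time of permanence from the primary logistic model.
- Adjust only for prespecified variables fixed before randomisation: the stratification factors (sex assigned at birth, educational level, current ART intake, history of ART abandonment) and baseline SMAQ adherence, which the enrolment form already collects. Code them sparingly: at the planning rates, 131 participants yield only about 131 × (0.10 + 0.20)/2 ≈ 20 non-adherent.
- State which estimate is primary, the unadjusted comparison or the baseline-adjusted odds ratio, and label the other as supportive.
- Keep permanence as the secondary outcome it already is. Use pick-ups and permanence only in an analysis labelled exploratory, or as auxiliary variables for missing week-16 data. There is no need to add pick-ups as a new outcome now that follow-up has ended.

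Cost: no new data. The data were in curation in February 2025, so the change should be documented before analysis. Ethical Considerations requires approval of amendments by both IRBs and an update on the trial registry.
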